|------------------|------------------------------------------------|
| PT               | Preferred Term                                 |
| SAE              | Serious Adverse Events                         |
| SAP              | Statistical Analysis Plan                      |
| SARS             | Severe Acute Respiratory Syndrome              |
| SMC              | Safety Monitoring Committee                    |
| SmPC             | Summary of Product Characteristics             |
| SOC              | System Organ Class                             |
| SOP              | Standard Operating Procedures                  |
| SUSAR            | Suspected Unexpected Serious Adverse Reactions |
| T 1/2 | Half-life                                      |
| TID              | Ter in die, three times a day                  |
| t max | Time of maximum analyte concentration          |
| ULN              | Upper Limit Normal                             |

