| Serology                                                                  | X            |                      |                  |                |                |                |                |                |                |   |                 |
| SARS-CoV2-test                                                            | X            |                      |                  |                |                |                |                |                |                |   |                 |
| Safety lab
(haematology, clinical
chemistry
incl.coagulation,
urinalysis) | X            | X                    |                  |                | X              |                |                |                |                | X | X               |
| Administration of
niclosamide solution
(TID)                                    |              |                      | X                | X              | X              | X              | X              | X              | X              |   |                 |
| Pharmakokinetic
samples, niclosamide
solution                                   |              |                      | X    | X  | X  | X  | X  | X  | X  |   |                 |
| SAE / AE ConMed
reporting                                                          | X            | X                    | X                | X              | X              | X              | X              | X              | X              | X | X               |

Serology: Anti HCV Ab, HBs Ag, Anti, HIV1 and HIV2 PK: predose, 30 min, 60 min, 90 min, 2h, 4h, 6h, 8h, 12h, 24h post dose vital signs: pre-dose, 1.0, 2.0, 4.0, 8.0 and 12 h SARS CoV2-test will be done before domiciling as close to the baseline check-in as possible ECG, body temperature: pre-dose and 3 h post-dose PK at trough level

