### 1.3. Rationale for Dose Selection

The niclosamide treatment regimen against tape worms comprises a 2 g dose at day 1 followed by 6 days of 1 g for individuals aged >6 years. Intestinal resorption is low, and the bioavailability is on average 10% (although there is a high variability).

Part A of the study consists of single ascending doses of the new oral solution with three planned cohorts (A1, A2, A3). The initial dose of 200 mg, in case of assuming 100% absorption, corresponds to the systemic exposure of the chewing tablet of 2000 mg assuming a bioavailability of 10%. However, complete (100%) absorption of the oral solution is highly unlikely since niclosamide is likely to be metabolized already in the intestine. The starting dose of 200 mg is therefore considered safe. The next higher dose of 600 mg is a threefold increase from the starting dose. The final dose of 1600 mg is limited by the solution excipients which are known to give rise to diarrhea at higher volumes. Both the 600 mg and 1600 mg cohorts will only be started if the previous dose is safe and the pre-defined plasma level of above 5  $\mu$ M (approx. 1.6  $\mu$ g/ml) after 8 hours has not been reached. If the 1600 mg dose is not tolerated, there is an option to repeat the cohort with a lower dose of 1200 mg. The last cohort will be repeated under fed conditions to investigate a possible food effect.

The first subject in each cohort will be the sentinel subject receiving an open label niclosamide solution administration.

Overall, the proposed SAD design for this study mimics conventional FIH studies, and thus, seems to be a suitably conservative approach for testing the niclosamide solution formulation.

Part B of the study compares the highest acceptable dose in Part A (1600 mg oral solution) with the highest approved dose of the chewing tablet (2000 mg) given as a QD dosing regimen under fed conditions to determine the relative bioavailability of the new oral solution formulation.

The chosen dose will not exceed the maximum tolerable dose in Part A.

Part C investigate safety and PK of the niclosamide solution over a period of 7 days.

This part consists of three groups: Group 1, 1200 mg niclosamide solution administered once daily, Group 2, 1600 mg niclosamide solution administered once daily and Group 3, placebo.

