The medium dose of niclosamide has been added to have the possibility to stop dosing in the 1600 mg group and continue with 1200 mg dosing in case of intolerable side effects, which may occur by accumulation of the excipient PEG-400 in the gut.

Accumulation of niclosamide is not expected after multiple dosing considering the plasma concentration-time profiles observed in Part A of the study.

Niclosamide solution will be administered once daily under fed conditions.

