### **Part C: Multiple dose part with the niclosamide solution**

The multiple dose part (Part C) will start in parallel to Part B since Part B will only be performed to get information about the relative bioavailability of the niclosamide solution compared to the approved niclosamide chewing tablets. The chosen dose of the niclosamide solution in Part B is identical with the highest dose given under fed conditions in Part A of this study, which was safe and well tolerated. Thus, there is no additional risk to start with Part C in parallel to Part B.

Part C is comprised of a screening visit (between Day -21 and Day -2), a baseline evaluation (Day -1), a multiple dose treatment period (Day 1 through Day 7, discharge on Day 8) with OD dosing of niclosamide solution and one EOS visit between Day 10 and Day 12.

Part C consists of three parallel groups:

Group 1: 1200 mg niclosamide solution (n=4)

Group 2: 1600 mg niclosamide solution (n=4)

Group 3: Placebo (n=4)

The high dose of niclosamide solution can be stopped and continue with the medium dose in the subsequent subjects, if moderate to severe GI side effects occur most likely due to an accumulation of the excipient PEG-400 in the gut.

Approximately 12 subjects (4/group) will be enrolled in this part of the study, who receive the niclosamide solution (1200 mg and 1600 mg QD) or placebo over a treatment period of 7 days. The dose of the niclosamide solution depends on the safety and PK results of Part A and will not exceed 1600 mg QD.

Subjects will remain domiciled in the study site from Day -1 until the Day 8 (24h post dose) and until all assessments have been completed. Subjects will be allowed to leave the study center on Day 8 at the discretion of the Investigator, if there are no prohibitive safety findings. The subjects will be asked to return to the study site for the EOS assessments on Day 10 (+2 days). The EOS evaluation has also to be performed if a subject prematurely terminates the study for any reason.

All baseline safety evaluations results must be available prior to dosing.

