### Part B (relative bioavailability compared to chewing tablets)

Planned doses:

- Single dose of 1600 mg oral niclosamide solution (highest dose that was tested to be safe and tolerable in Part A) under fed conditions
- Single dose of 2000 mg niclosamide chewing tablets as multiples of 500 mg chewing tablets under fed conditions

Part C (multiple doses of the niclosamide solution)

- Multiple doses of 1200 mg oral niclosamide solution under fed conditions over 7 days
- Multiple doses of 1600 mg oral niclosamide solution under fed conditions over 7 days
- Placebo under fed conditions over 7 days

In all cohorts, study drug will be administered at the study site.

In Part A cohorts, subjects must have fasted overnight for at least 9 hours before study drug intake. Intake of water is not allowed from approximately 2 hours before until approximately 2 hours after study drug intake (except for the non-carbonated water required for study drug intake). Standard lunch will be served within 15 to 30 minutes after the 4-hour PK sampling on Day 1 and in Part B also on Day 3. The lunch should be of the same composition for all subjects on Day 1. The standard lunches should be ingested entirely within 30 minutes. If this is not possible, the approximate percentage of the consumed food should be documented.

A standard snack and a standard dinner will be served approximately 7 and 10 hours postdose, respectively. This snack and dinner should be of the same composition for all subjects.

In the fed dose cohort in Part A (cohort 3) and in Part B and Part C, following overnight fast of at least 9 hours, subjects should start a high fat meal 30 minutes prior to the study drug administration at the study site between 7.30 and 10.00 AM. This meal should contain approximately 800 to 1000 calories and should derive approximately 150, 250, and 500 to 600 calories from protein, carbohydrate, and fat, respectively (according to the FDA guidance for industry). Subjects should consume the entire meal within 30 minutes. If this is not possible, the approximate percentage of the consumed food should be documented. Within 10 minutes after completing breakfast, but no more than 30 minutes from the start of their high fat meal, study drug will be administered with approximately 240 mL of non-carbonated water. Thereafter, subjects should receive standardized meals scheduled at the same time in each cohort of the study.

[figure not shown]

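### The Part C schedule (Table 3) labels niclosamide dosing as three times a day, while Sections 1.3 and 3.1 fix it at once daily with a 1600 mg daily ceiling

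*Protocol*

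**What the plan says.** Table 3 of the protocol (Schedule of Assessments, Part C) has a dosing row labelled "Administration of niclosamide solution (TID" (the bracket closes after TID), with a mark on each of Days 1 to 7. The abbreviation list expands TID as "Ter in die, three times a day".

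The body text says otherwise:

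- Section 1.3 gives the 1200 mg group once-daily dosing and continues: "Group 2, 1600 mg niclosamide solution administered once daily and Group 3, placebo". It then repeats: "Niclosamide solution will be administered once daily under fed conditions".
- Section 3.1, Part C, describes a Day 1 to Day 7 treatment period "with OD dosing of niclosamide solution", gives both dose levels as QD, and sets a limit: "The dose of the niclosamide solution depends on the safety and PK results of Part A and will not exceed 1600 mg QD".

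Two other places give the Part C doses without any frequency. Section 6.1.1 lists "Multiple doses of 1600 mg oral niclosamide solution under fed conditions over 7 days" and a matching line for 1200 mg. The Part C paragraph of the synopsis gives the group doses and the 7-day period only.

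**The concern.** One current table prescribes three administrations a day and two current sections prescribe one. Both cannot be right. Table 3 is operative text, so this is not a mismatch between an amendment log and the document it amends.

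The error runs in the unsafe direction. The subjects are healthy volunteers, and the protocol limits the top dose because of its vehicle: "The final dose of 1600 mg is limited by the solution excipients which are known to give rise to diarrhea at higher volumes". Sections 1.3 and 3.4 also provide for stepping down from 1600 mg once daily if PEG-400 accumulates in the gut and side effects follow. Three administrations a day would work against that precaution.

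The places where staff might look for a correction do not print one. The Part C dosing lines in Section 6.1.1 and the synopsis name no frequency. TID is in the abbreviation list, but QD and OD, which Section 3.1 uses interchangeably for once daily, are not.

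**Working it through.** **Which frequency is intended?** The places that bear on it, side by side:

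| Place in the protocol | Frequency stated or implied for Part C |
|---|---|
| Table 3, dosing row | TID |
| Abbreviations | TID means three times a day |
| Section 1.3, group list and closing line | once daily |
| Section 3.1, Part C | OD; QD; ceiling 1600 mg QD |
| Section 6.1.1, Part C dose lines | none printed |
| Section 6.1.1, fed-dosing procedure | overnight fast of at least 9 hours, then a high-fat meal and the dose, with a 7.30 to 10.00 AM window: one dose a day |
| Table 3, footnotes 2 and 6 | full 24-hour profile on Days 1 and 7, trough sample on Days 2 to 6 |
| Synopsis, Part C | none printed |

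Apart from the label itself, nothing in the current Part C text supports three doses a day. As context on intent only, the Amendment 2 log records that Part C moved from TID to QD, and Table 3 is not among the sections it lists for that change. A leftover label fits this.

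**Does the label fit the table's own sampling?** Footnote 2 has 10 time points: predose, 0.5, 1, 1.5, 2, 4, 6, 8, 12 and 24 hours. The protocol gives no dose interval for TID. Assuming 8 hours, doses would fall at 0, 8 and 16 hours, and the 12-hour and 24-hour samples (2 of 10) would follow a later dose. Under once-daily dosing all 10 describe one dose.

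**Size of the discrepancy if the label is read literally.** Inputs: group doses of 1200 mg and 1600 mg (Section 3.1), solution strength 40 mg/mL (Section 6.1), ceiling 1600 mg per day (Section 3.1). Assumption: the full group dose is given at each administration; Table 3 itself states no dose.

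Daily dose = administrations per day × group dose. Daily volume = daily dose / 40 mg/mL.

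| Group | Once daily (body text) | Three times daily (Table 3 label) | Ratio to the 1600 mg ceiling under the label |
|---|---|---|---|
| 1200 mg | 1200 mg; 1200/40 = 30 mL | 3 × 1200 = 3600 mg; 3600/40 = 90 mL | 3600/1600 = 2.25 |
| 1600 mg | 1600 mg; 1600/40 = 40 mL | 3 × 1600 = 4800 mg; 4800/40 = 120 mL | 4800/1600 = 3 |

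Once-daily dosing keeps both groups at or below the ceiling. The literal label takes both above it.

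**A side observation.** The 24-hour sample of the Day 7 profile falls on Day 8, where the Table 3 PK cell is blank. Footnote 2 already specifies the sample, so this is editorial. Tables 1 and 2 do mark their next-day samples.

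**The case against.** The strongest reply is that the protocol settles the matter itself. Once daily appears repeatedly in Sections 1.3 and 3.1, in words as well as abbreviations. The procedure in Section 6.1.1 cannot be carried out three times a day, so that section settles the frequency in practice even though it prints none. Section 5 points to Tables 1 to 3 for the timing of assessments, and the heading on dose and time of administration is Section 6.1.1. Table 3 carries no dose, so nobody could dose from it alone. Subjects are domiciled and dosed by staff at a single site. The protocol does not say how dosing worksheets, drug supply or eCRF pages are prepared, so building them from Table 3 is conjecture. The worst-case volumes are excluded by the ceiling.

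Most of this stands, and it limits the weight of the point. A careful reader reaches once daily, and the large volumes should not be read as an expected outcome. The abbreviation entries and the Day 8 cell are editorial.

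It does not make the label harmless. Table 3 is the Part C schedule, it includes a dosing row, and that row names a wrong frequency. Correcting it by inference requires the reader to go to other sections and decide which text prevails. For a dosing frequency in healthy volunteers, that should not be left to the reader.

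**Conclusion.** The label in Table 3 is wrong as written, and once daily is the intended regimen. This should be fixed, but it is not a flaw in the design.

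Read literally, the discrepancy is a factor of three in daily dose and in solution volume: 4800 mg against 1600 mg, and 3600 mg against 1200 mg. That assumes the full group dose at each administration, which Table 3 does not state and the 1600 mg ceiling rules out. The practical exposure is a site error arising from documents prepared from the table; the protocol gives no basis for putting a probability on it. The steady-state PK analysis is not at stake, because both the text and the sampling scheme describe once-daily dosing. The study plans no formal hypothesis test, and no sample-size figure depends on this.

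**What to change.** - In the Table 3 dosing row, replace TID with QD.
- Add the words once daily to the Part C lines of Section 6.1.1 and to the Part C paragraph of the synopsis.
- Use a single term for once daily in place of the OD and QD in Section 3.1, and enter it in the abbreviation list.
- Notify the site before the first Part C dose, and check any dosing worksheet, supply plan or eCRF dosing page already prepared.
- Minor: mark the Day 8 PK cell in Table 3 for the 24-hour sample of the Day 7 profile.

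The cost is one word and one cell in Table 3, two short insertions, one consistent abbreviation with its entry, and a site notification. Design, doses, sampling times and sample size stay as they are.

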# 1. Introduction

## 1.1. Background

At the beginning of the year 2020, an epidemic caused by the new coronavirus SARS-CoV-2 causing COVID-19 began in China (Zhu et al. 2020). A total of 215 countries have reported infections. The World Health Organisation (WHO) declared the coronavirus epidemic a pandemic on 11 March 2020. This is the first pandemic known to be caused by the emergence of a new coronavirus. Since 31 December 2019 and as of 15 July 2020, 13299163 cases of COVID-19 have been reported, including 578319 deaths (Up to date, most cases have emerged in Europe (more than 2 million confirmed cases) and in the US (more than 3 million cases) (<https://www.ecdc.europa.eu/en/geographical-distribution-2019-ncov-cases>)).

The SARS-CoV-2 virus is a beta-coronavirus, like MERS-CoV and SARS-CoV. All three of these viruses have their origins in bats.

Several trials have been set up in the last weeks to test various antiviral substances like remdesivir (a substance originally developed against Ebola virus) that showed activity against SARS-CoV-2 in vitro and against SARS and MERS-CoV both in vitro and in animal studies (Sheahan et al. 2017, Wang et al. 2020). That drug received a conditional marketing authorization in Europe which was based on rolling review of supporting data that began in April 2020.

Other drugs are under investigation. However, to date no proven pharmacological regime exist that could improve the natural course of the disease.

People with COVID-19 have had a wide range of symptoms reported – ranging from mild symptoms to severe illness. Symptoms may appear 2-14 days after exposure to the virus.

This study will primarily investigate the safety and pharmacokinetics of a new oral solution of niclosamide, a potential antiviral substance. The new formulation is being developed to be used in subsequent studies in combination with camostat for the treatment of COVID-19. Niclosamide is currently used in antihelminthic therapy and was shown to be effective in vitro against SARS-CoV-2 infections by activating cellular autophagy processes. In Part C of the study, niclosamide will be administered in a multiple dose regimen in healthy volunteers.

### **Niclosamide (Yomesan®):**

Niclosamide is an approved drug for the treatment of tapeworm infection for more than 50 years. The highest approved dose of niclosamide is 2000 mg on Day 1, followed by 1000 mg/d up to six days. In addition to its current use as a treatment of tapeworm infection, niclosamide has also found a novel role in cancer therapy and as an antiviral agent (Xu et al. 2020).

Drug-induced modulations of cellular pathways like autophagy were shown to broadly affect virus growth (Lundi et al. 2014; Pfeifferle et al. 2011). Researchers from the Institute of Virology at Charité – Universitätsmedizin Berlin recently found that highly pathogenic MERS-CoV limits the cellular recycling process (autophagy) via Beclin-1 degradation and that stabilization of the autophagy-initiating Beclin-1 protein effectively reduced propagation of MERS-CoV (Gassen et al. 2014). Niclosamide was the most promising Beclin-1-stabilizing drug reducing MERS-CoV growth *in vitro* up to 28,000-fold. In ensuing experiments, it was shown that SARS-CoV-2, similar to MERS-CoV, limits autophagy. Furthermore, niclosamide reduced SARS-CoV-2 propagation up to 16,000-fold in cell cultures. The  $IC_{50}$  of niclosamide was 0.17  $\mu$ M ( $R^2= 0.63$ ) at 48 hours post SARS-CoV-2 infection, being well below the observed niclosamide serum levels of 0.76-18.35  $\mu$ M upon oral uptake of 2000 mg. These observations were recently confirmed and pre-published by a Korean research team (Jeon et al. 2020). In a recent study performed by the team of C. Drosten (Dept. of Virology, Charité – Universitätsmedizin Berlin) it was confirmed that niclosamide also potently inhibits SARS-CoV-2 (Hoffmann et al. 2020).

[figure not shown]

Based on EC50 data from these experiments, a plasma level of 3-5 µM could be an effective COVID-19 treatment. Niclosamide is currently marketed as chewing tablets only. The tablets are used to treat intestinal worm infections and therefore formulated to minimize systemic absorption.

An oral solution has been developed with the aim to achieve higher and more reproducible plasma levels.

### **Safety Profile of Niclosamide:**

The safety profile of niclosamide is well known from the treatment of tapeworm infection and from treatment in other not approved indications.

According to the SmPC of niclosamide, the following adverse drug reactions are known from spontaneous reporting: Hypersensitivity reactions (e.g. erythema, pruritus, and exanthema), dizziness, cyanosis, gastrointestinal symptoms such as such as nausea, retching, abdominal pain and diarrhea.

In a prostate cancer study, a dose of 3000 mg in combination with enzalutamide led to prolonged grade 3 nausea, vomiting, diarrhea and colitis.

Overall, doses up to 2000 mg niclosamide were safe and well tolerated.

### **Niclosamide solution**

A niclosamide solution has been developed with the aim to achieve higher and more reproducible plasma levels compared to the already marketed niclosamide chewing tablet. In contrast to the chewing tablet, which is formulated to minimize systemic absorption, the new oral solution is being developed to reach systemic exposure which is sufficient to be effective in the treatment of COVID-19 in combination with camostat.

The solution consists of polyethyleneglycol 400 as the main ingredient and solvent for niclosamide. It also contains polysorbate 20 as a surfactant and levomenthol as flavor. All excipients are well known and widely used in drug development. All excipients are described in the European Pharmacopoeia. Polyethylene glycol 400 is known to be a safe and has been used for many drug substances since the 1950ies (Smyth et al. 1950 and 1955, Tusing et al. 1954). It is described in the "Handbook of Pharmaceutical Excipients". The WHO has set an acceptable daily intake of polyethylene glycols at up to 10 mg/kg body weight (World Health Organ Tech Rep Ser 1980, No 648) which is far in excess of the maximum proposed doses here. Polyethylene glycols are known drug substances themselves, used to treat obstipation. Diarrhea would therefore be the only adverse event to be expected.

This study is primarily designed to investigate the safety and pharmacokinetics of a novel niclosamide solution after single and multiple dose administration. The new formulation is being developed to be used in subsequent studies in combination with camostat for the treatment of COVID-19.

